### Strand 1 and 2: Surveys (Quantitative)

Surveys will be administered on 2 occasions, separated by several months. First, a baseline survey will be conducted across all 4 participating hospitals within the first month after initiation of the study, with the second follow-up survey conducted between 5 and 11 months after initiation. In the intervening period, the Respectful Workplace Workshops will be conducted at 2 of the 4 hospitals.

This component of the study is designed to investigate NGNs’, RNs’, and senior RNs’ experiences and perceptions of negative workplace behaviors occurring in medical and surgical wards as well as whether there are any observable differences over the period of the study between the two sites where the workshops will be conducted as compared with the other two sites. The survey will also examine the ways of coping by respondents after being exposed to negative workplace behaviors. The initial survey will capture data from the NGNs within their first 3 months of employment, when they are reportedly most vulnerable and require most support [32]. Participants do not need to complete the strand 1 survey or attend the workshops to participate in the strand 2 survey.

With careful consideration of the content and layout, the questionnaire was informed by a literature search to identify the validated instruments. The recruitment package consists of multiple parts, as follows:

A participant information statement detailing the nature of the study according to the ethics requirementsDemographic and background questionsNegative Acts Questionnaire—Revised (NAQ-R) [33]Purpose-designed self-assessment of exposure to bullying and incivility questionsPurpose-designed questions informed by the learning outcomes of the workshopsManagement of bullying and incivility questions (NUMs only)Ways of Coping Questionnaire (WCQ) [34]A separate consent form to return for volunteering to participate in a subsequent interview

Permission was granted for the use of the NAQ-R [33], which was originally designed to measure exposure to bullying in the workplace. This instrument consists of 22 items measuring exposure to negative workplace behaviors, with response alternatives on a 5-point Likert-type scale, where the higher the score, the greater the frequency of exposure to negative acts. The Cronbach α for the NAQ-R is .95 for the total scale, meaning that it has a high level of consistency between the questionnaire items. The NAQ-R has 3 subscales: person-related bullying, work-related bullying, and physically intimidating bullying [33]. Two additional items will be added to the NAQ-R to assess the perceived degree to which patient care is compromised or obstructed and whether respondents felt that they have been isolated from supportive peers. The addition of these items was justified by evidence from a recent integrative review of relevant literature [2].

The purpose-designed self-assessment of exposure to bullying questions also uses a 5-point Likert-type scale response, where higher scores indicate increased exposure. Before answering this section, respondents are asked to consider the definition of *workplace bullying* from the New South Wales Ministry of Health [35]. Participants were also asked whether they had been exposed to incivility at work over the previous month, with response alternatives as follows: 1=no; 2=yes, but only rarely; 3=yes, now and then; 4=yes, several times per week; and 5=yes, almost daily. For this question, the definition of *workplace incivility* is “lower level, subtle forms of workplace mistreatment.” Examples include: *having your ideas or opinions dismissed*; *having derogatory or demeaning remarks made about your work*; *eye rolling*; *feeling belittled or humiliated*; *and being stared at*, *watched*, *or being excluded from social activities*.

Participants are asked to identify the designation of the *perpetrator* of the negative workplace behavior to which they had been exposed. Response options are as follows: manager, colleagues (other RNs), endorsed enrolled nurses, assistants in nursing, patients, doctors, students, and others. The turnover intentions of participants will be measured on a Likert scale (strongly disagree, disagree, unsure, agree, and strongly agree) in response to the statement that “the impacts of bullying and incivility in my workplace make me think about leaving my current position.” Likert scale responses are also used as a self-assessment measure of participants’ capabilities to respond to and manage bullying and incivility. Participants are asked about policy awareness and their perceived capacity to use resolution pathways, challenge disrespectful behavior, and know when to escalate and ask for assistance.

The WCQ is a 66-item instrument that is designed to examine coping processes in stressful encounters [34]. Revised in 1985, it is in the public domain and no special permission was required for its use [34]. Respondents are asked to indicate to what extent they use particular strategies to cope when exposed to negative workplace behavior using the following responses: 0=not used, 1=used somewhat, 2=used quite a bit, and 3=used a great deal. The WCQ consists of 8 subdomains, including 1 problem-focused scale, 6 emotion-focused scales, and an eighth scale containing both problem-focused and emotion-focused items [34]. The Cronbach α for each scale ranged from .61 to .79 [34].

The NGNs, RNs, and senior RNs will be invited to complete the surveys on either hardcopy or on the internet via *REDCap* (Hunter Medical Research Institute, 2020), which is a secure web-based application for building and managing web-based surveys and databases. Details of how to access the web-based survey will be displayed on information posters in the wards or units, with responses uploaded automatically to the database. The web-based option allows nurses to participate without the risk of being seen taking a hardcopy from the ward or unit, whereas the alternative hardcopy option considers limitations in access to the internet. Hardcopies can be returned anonymously by either depositing them into brightly colored, sealed boxes in the staff rooms or sending them directly to the research team in the self-addressed, reply paid envelopes. To increase the response rates, all potential respondents will receive an email reminder from the new graduate coordinator at their particular hospital at 2 and 4 weeks after the initial survey distribution.

### Strand 3: Interviews (Qualitative)

The qualitative research component adheres to the COREQ (Consolidated Criteria for Reporting Qualitative Studies) [36]. A completed COREQ checklist has been appended as Multimedia Appendix 1 to this study.

The qualitative strand occurring after preliminary quantitative data analysis aims to broaden and deepen the understanding of nurses’ experiences and perceptions of workplace behavior by allowing exploration through dialog in semistructured, one-on-one interviews [27]. To participate, informants will be purposively selected to be representative of nursing roles and hospital sites from the consenting participants in strand 1 (Figure 1). The informants need not attend the workshops to participate in an interview but must work on one of the wards included in the sampling frame. The interviews are expected to last up to 1 hour and will be audio-recorded, then transcribed verbatim by a transcription service with which the university has a confidentiality agreement for subsequent content analysis. The sample size in the qualitative strand cannot be postulated, as it will be determined by developing theoretical categories [37]. Data collection and analysis will occur concurrently, and it is anticipated that interviews will continue until such time that no *new theoretical insights nor new properties of core theoretical categories emerge* [37].

### Quantitative Data Analysis

The quantitative data will be analyzed using Stata 14 (TM; StataCorp LP), a statistical software that enables users to analyze, manage, and produce graphical presentations of data [38]. Participant characteristics will be summarized separately for intervention and control sites. Differences between groups for categorical variables will be assessed using chi-squared tests (or Fisher exact, the nonparametric equivalent) and Student's *t* tests for continuous variables. Differences between intervention and control sites in exposure to bullying (as assessed by the NAQ-R) and ways of coping (as assessed by the WCQ) will be assessed for all nurses at strand 2. Statistician support will be pursued to assist with analysis.

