### Setting, Sampling, and Participants

Study setting, sampling, and participant recruitment will be based on the inclusion criteria pertinent to the research aims [30]. To minimize selection and participant bias, comprehensive and rigorous criteria have been developed. Potential hospitals and units for inclusion were selected in consultation with the Respectful Workplace Team, the members of which are employed in the LHD to deliver Respectful Workplace Workshops in the hospitals. The selection of hospitals and units was based on the presence of minimal or no previous attendance by nurses at the Respectful Workplace Workshops. A total of 9 employees across the 4 hospitals were identified as having potentially attended the workshops previously at other hospitals within the health district. The hospitals chosen are of similar size, with similar service availability and case mix. Regional hospitals were selected because the phenomenon under investigation is of significant concern in nonmetropolitan locations, where ongoing staffing and recruitment issues exist [31]. Being in the same LHD, all 4 hospitals have the same centralized executive leadership, are subject to the same bullying and negative workplace behavior policies, and are subject to the same human research ethics committee governance processes. In total, 2 of the 4 hospitals were assigned to have the Respectful Workplace Workshops delivered within the 6-month study period; these hospitals (A and B) are referred to as the *intervention sites* in Figure 1. The other 2 hospitals did not have the workshop delivered until after data collection of strands 2 and 3 was completed. Those hospitals (C and D) are referred to as the *control sites* in Figure 1.

This study included 12 wards or units across 4 nonmetropolitan, regional acute care hospitals within the same New South Wales LHD. The units were selected on the basis that they were general medical or surgical wards, where most NGNs were employed.

Targeted study participants may be categorized as follows:

NGNs in their first 12 months of practice following the completion of a Bachelor of Nursing degree.RNs who had been employed for more than 1 year at a minimum of 0.6 full-time equivalent.Senior RNs are employed in permanent leadership roles, who have managerial responsibilities for other staff members and patients, including NUMs, CNEs, and clinical nurse specialists.

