Nursing staff known to have attended the workshops previously will be excluded from selection and others who indicate in the initial survey screening questions that they had previously attended the workshop will also be excluded from the data analysis. Owing to the relatively low number of previously exposed participants spread across 12 wards or units, the risk of contamination bias at a site level was considered minimal.

The participants will be allocated into clusters according to hospitals at which they are working; thus, they will be employed at hospitals where the workshops were either delivered or not delivered. Nested sampling will be undertaken for the qualitative and quantitative components of the study. The sample of the qualitative component is a subset of those who participated in the quantitative components. Survey participants will be a volunteer sample of nursing staff working in the medical and surgical wards in all 4 participating hospitals. The sample for the qualitative component of the study will be purposively chosen from survey respondents who will volunteer to be interviewed to represent the roles of the nurses and sites where they are working.

The total target population is 230 at the time of writing this paper, which includes 64 NGNs, 154 other RNs, and 12 senior RNs with managerial roles. Assuming a 30% response rate (n=69), 5% type 1 error, and 80% power to detect an effect size equivalent to 0.7 of the SD, it is anticipated that it will be necessary to recruit 35 participants from the hospitals where the Respectful Workplace Workshops will be delivered and 35 from those where no workshops are conducted.

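### Workshops are allocated by hospital (2 v 2), yet the only between-group tests named treat nurses as independent; used on the outcomes, they would not hold the 5% error rate

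*Protocol article*

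**What the plan says.** **Allocation.** Under *Setting, Sampling, and Participants*: "In total, 2 of the 4 hospitals were assigned to have the Respectful Workplace Workshops delivered within the 6-month study period". The other two hospitals receive the workshops only after data collection. The same section says: "The participants will be allocated into clusters according to hospitals at which they are working". There is a further level below hospital: "This study included 12 wards or units across 4 nonmetropolitan, regional acute care hospitals". No randomisation is described; sites were chosen in consultation with the team that delivers the workshops.

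**Planning.** The sample size, in the same section, assumes a 5% type 1 error and "80% power to detect an effect size equivalent to 0.7 of the SD", and arrives at 35 respondents from workshop hospitals and 35 from the others.

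**Analysis.** Under *Quantitative Data Analysis*, a sentence on summarising participant characteristics is followed by: "Differences between groups for categorical variables will be assessed using chi-squared tests (or Fisher exact, the nonparametric equivalent"), with Student's t "tests for continuous variables". The next sentence says that site differences on the NAQ-R and WCQ "will be assessed for all nurses at strand 2", and names no test. The section ends by saying that a statistician's help will be sought.

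No ICC, design effect, mixed model, GEE, cluster-robust variance or hospital-level analysis appears anywhere in the article.

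**The concern.** Chi-squared, Fisher and two-sample t tests assume that each nurse is an independent observation. Here the intervention is given to a hospital, and the outcome, exposure to negative behaviour at work, is largely a feature of the shared workplace. The protocol says as much in *Principal Findings*: it describes wards where staff know one another well and long-serving staff set the tone, and it places the research at the organisational level more than the individual.

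If responses within a hospital or ward are positively correlated, the named tests leave that variance out of the error term. Confidence intervals are then too narrow and p values too small, and an ordinary difference between two pairs of hospitals can be reported as a workshop effect. That matters because the article promises to assess the workshops' effectiveness and expects its evidence to inform practice and policy.

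**Working it through.** **Inputs from the protocol.** 2 v 2 hospitals; 12 wards; 35 v 35 respondents; effect 0.7 SD; 80% power; 5% type 1 error (two-sided assumed, since the sides are not stated).

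**Assumptions.** ICC 0.01 to 0.10, because the protocol gives none; equal response by hospital, so m = 35/2 = 17.5; for the ward-only case, six wards per group with about six respondents each.

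**1. Reproduce the plan's figure.** n per group = 2 × (1.96 + 0.842)² / 0.7² = 32.04, rounded up to 33. The t-based calculation gives 33.02, so 34. At 35 per group the individual-level power is 83% (normal) or 82% (t). A one-sided calculation gives 26. The stated 35 is therefore a two-sided, individual-level figure with no visible allowance for clustering.

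**2. Type 1 error of the unadjusted test, clustering by hospital.** Design effect DE = 1 + (m − 1) × ICC. The true standard error is √DE times the unadjusted one. Actual error = 2 × [1 − Φ(1.96/√DE)]. For example, at ICC 0.05, DE = 1 + 16.5 × 0.05 = 1.825, √DE = 1.351, and the error is 14.7%. The formula was checked by simulating the t test with no true effect (40,000 runs per row, hospitals of 18 and 17 in each group).

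| Assumed ICC | DE | SE ratio | Type 1 error, formula | Simulated |
|---|---|---|---|---|
| 0 | 1.00 | 1.00 | 5.0% | 5.0% |
| 0.01 | 1.17 | 1.08 | 6.9% | 6.7% |
| 0.02 | 1.33 | 1.15 | 8.9% | 8.9% |
| 0.05 | 1.83 | 1.35 | 14.7% | 14.8% |
| 0.10 | 2.65 | 1.63 | 22.9% | 23.6% |

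**3. Clustering by ward only.** With six respondents per ward, DE = 1 + 5 × ICC = 1.10, 1.25 and 1.50 at ICC 0.02, 0.05 and 0.10. The same formula gives 6.2%, 8.0% and 11.0%; simulation gives 6.1%, 7.9% and 11.3%.

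**4. Power at 0.7 SD with 35 v 35.**

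| Assumed ICC | Design effect only (normal) | t test on four hospital means (2 df) |
|---|---|---|
| 0 | 83% | 37% |
| 0.01 | 77% | 34% |
| 0.02 | 72% | 31% |
| 0.05 | 58% | 24% |
| 0.10 | 44% | 19% |

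Much of the loss in the last column comes from having only 2 degrees of freedom, whatever the ICC.

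**5. What a hospital-level interval would look like.** Variance of a hospital mean in SD units = ICC + (1 − ICC)/17.5. At ICC 0.05 this is 0.05 + 0.0543 = 0.1043. The difference between two averages of two hospitals has the same variance, so SE = 0.323, and the half-width is 4.303 × 0.323 = 1.39 SD. The unadjusted half-width is about 1.995 × √(2/35) = 0.48 SD.

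**The case against.** **The test sentence may cover only the characteristics table.** It follows directly on the sentence about participant characteristics, and the outcome sentence names no test. A reader might infer that the protocol prescribes t tests for the NAQ-R and WCQ; the text does not say so. This part of the objection stands, and the point must be put conditionally. It does not remove the concern: no other test is named, the outcome sentence comes next with no change of method, and the sample size is what a two-sample t test of nurses would need.

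**A condensed article may leave the outcome model to an analysis plan.** It may, and silence alone would be no finding. Here, though, the article calls hospitals clusters while its named tests and its power statement both ignore them. Seeking statistical support does not settle the method.

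**The size rests on an assumed ICC.** Correct. A reader might take 23% as this study's error rate; it is the upper end of an assumed range, and ward-only clustering at ICC 0.02 gives about 6%. Only the direction is independent of the ICC, provided that it is positive.

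**A mixed model would repair it.** This is tempting but not supported. In a strand 2 comparison, a hospital fixed effect is collinear with group. An arm-by-period model can be fitted, but it leaves hospital-specific change over time out of the error term. Simulated under the null (12 wards, six fresh respondents per ward per period, 20,000 runs), such a model with a hospital fixed effect and a ward random intercept had a type 1 error of 9%, 15% and 25% when the hospital-by-period variance share was 0.02, 0.05 and 0.10. *Potential Limitations* itself foresees staff changes or a change of manager during the study.

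**No test rescues 2 v 2.** True: there are 6 ways to choose 2 of 4 hospitals, so a hospital-level permutation test cannot give a two-sided p below 2/6 = 0.33. That is a limit of the design, not a measure of the t test's error, and it is a reason to restrict the claim.

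**Conclusion.** The point holds in conditional form. The protocol allocates by hospital, and the only between-group tests that it names, like its sample size, assume independent nurses. If those tests are applied to the NAQ-R and WCQ at strand 2, any positive ICC makes the standard errors too small. At assumed ICCs of 0.02 to 0.10 the nominal 5% becomes about 9% to 23% with hospital clustering and about 6% to 11% with ward clustering only.

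The stated 80% power does not survive either. At 35 per group it is 77% or lower from ICC 0.01 upward on the design effect alone, and 19% to 34% for a 2-df hospital-level test across ICC 0.01 to 0.10. These figures assume equal response across hospitals and, for the ward case, an even split of wards. Correcting the standard error would not remove confounding from non-random assignment of hospitals.

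**What to change.** 1. State the method for the NAQ-R and WCQ comparison, and do not use unadjusted individual-level t, chi-squared or Fisher tests for it.
2. Show each hospital's estimate. Compare the groups with an analysis that respects hospital as the unit of allocation and uses small-sample degrees of freedom, for example hospital-level summaries with about 2 df. Allow for ward clustering as well where ward is recorded. The article does not say that the anonymous surveys record ward, so this needs checking.
3. State that, with two non-randomised hospitals per group, the between-site result is an exploratory estimate with a confidence interval for these four hospitals, not a 5%-level test of workshop effectiveness.
4. Withdraw the 80% power claim, or state that it ignores clustering.
5. If an arm-by-period model is wanted, present it as an additional analysis, with its assumption of no hospital-specific change over time stated. It does not by itself repair the error rate.

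The cost is a change to the analysis and reporting text, with no new data for the hospital-level analysis. The downside is much wider intervals (about 1.4 SD against 0.5 SD half-width at ICC 0.05) and a weaker claim.

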### Qualitative Data Analysis

The qualitative data will be organized using NVivo software (version 11; QSR International) [39]. The data analysis process will be guided by the Straussian Grounded Theory (SGT) [40,41], the method of choice for researchers framing their research within the Social Worlds Theory [42]. The aim of SGT is to generate an *explanatory theory that closely approximates the reality it represents* [43] and explore not only the phenomenon but also how the actors involved respond to this phenomenon and the consequences of their actions [40]. The SGT method includes a 3-stage approach: open coding, axial coding, and selective coding [40,44]. In the initial stage of open coding, the researcher is immersed in the transcribed interview data line-by-line using constant comparison to identify the categories of data [40,44]. Constant comparison involves reading and rereading transcripts, constantly comparing similarities and differences and sorting data into categories [45]. The axial coding stage involves the identification of relationships between data categories [40,44]. One of the key features of SGT is using a coding paradigm to assist with analyzing, refining, and aligning categories [40]. In the final, selective coding stage, categories are refined and integrated, ultimately leading to a small number of core categories that will link directly to the data [40,44]. The researchers will ensure the trustworthiness of the study by considering the validity standards that ensure rigor, confirmability, credibility, dependability, and transferability [46].

### Data Integration

Owing to the separative approach to data analysis, where quantitative and qualitative data are collected and analyzed separately [47,48], the integration of data will occur in the interpretation phase to assimilate the 2 analyses of the phenomena [47-50]. This approach is known as meta-inference and is achieved through a narrative reporting process, writing both qualitative and quantitative findings together on a theme-by-theme or concept-by-concept basis [51]. There are inherent challenges in undertaking data integration in mixed methods studies, and there are few examples of mixed methods research integration [52]. Challenges include researchers’ experience and methodological preferences; the nature of the data and avoidance of placing greater emphasis to one set of findings over the other; the design and timing of the phases of the study; and publication requirements and the target audience [52].

